### 2.5. Sample Size and Power

Sample size is justified a priori following current recommendations [70], with all calculations derived analytically from noncentral *F*, t, and chi-square distributions at a two-tailed significance threshold of α = 0.05 and a target power of 1 − β = 0.80, reproducible in G*Power 3.1 (“ANOVA: Repeated measures, within factors”) and consistent with recent tutorials on power analysis for repeated-measures designs [63]. The primary test is a repeated-measures ANOVA (four within-subject levels) on each composite score. Assuming a correlation between repeated measurements of ρ = 0.50 (a typical value for repeated attitudinal ratings, to be verified in the pilot), the minimum sample is 24 participants for medium effects (*f* = 0.25) and 138 for small effects (*f* = 0.10); under the conservative assumption ρ = 0.30, these become 32 and 193, respectively. The minimum analyzable threshold is therefore set at *N* = 140 valid participants, sufficient to detect even small between-scenario effects under realistic conditions. Because these thresholds depend on ρ, an adaptive rule is pre-registered for the case in which the pilot estimate falls outside the assumed ρ = 0.30–0.50 range. The pilot returns $\hat{\rho }$ with a 95% confidence interval, and every threshold is recomputed at its lower bound, ρ_L_, which is the conservative choice. The number of valid participants required to detect *f* = 0.10 at power 0.80 is 274, 247, 220, 193, 165, and 138 for ρ_L_ = 0, 0.10, 0.20, 0.30, 0.40, and 0.50, respectively; an intermediate ρ_L_ is rounded down to the nearest tabulated value, so that the rule is fully determined in advance for any estimate the pilot can return. Two consequences follow. The recruitment target does not change because the requirement is a decreasing function of ρ and reaches only 274 in the theoretical worst case of ρ_L_ = 0; *N* = 300 preserves power ≥0.80 against small between-scenario effects for every value ρ can take, and the target is in any case set by the person-level analyses described below, which do not depend on ρ. The analytic floor does change: it is redefined as the value tabulated above for the observed ρ_L_, so that it remains at the pre-specified *N* = 140—rounded up from 138—only when ρ_L_ ≥ 0.50 and rises to 165, 193, 220, 247, or 274 as ρ_L_ falls to 0.40, 0.30, 0.20, 0.10, or 0. A ρ_L_ below 0.10 would in addition indicate that the composites are unstable across repetitions rather than that participants are inconsistent, and would therefore also trigger re-inspection of pilot reliability and of the measurement-invariance assumptions before the main study is launched. Any application of this rule, and the $\hat{\rho }$ that triggered it, will be recorded in the pre-registration and reported in the results article.

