After expected attrition is taken into account—approximately 85% of link visitors consenting, 96% of starters eligible after screening, 75% of eligible respondents completing (drop-out conservatively inflated to 25% given the 15–20 min repeated-block format), and 90% of submissions surviving quality-based exclusions [68]—approximately 545 link accesses (≈334 submitted questionnaires) are required to yield 300 valid responses (Table 3). The stopping rule is accrual-based: data collection continues until a minimum of 300 valid responses is reached; the absolute analytic floor is *N* = 140—or the higher value returned by the adaptive rule above, should the pilot estimate of ρ require it—below which the main study is not analyzed, and collection is extended. Drop-out between the first and last scenario blocks will be monitored by serial position across all four sequences as a fatigue indicator.

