
### 2.9. Statistical Analysis

#### 2.9.1. Primary Analyses

Each composite score (acceptability, trust, perceived risk) will be analyzed by a mixed repeated-measures ANOVA, with autonomy level (four scenarios) as the within-subjects factor and presentation sequence (four Williams sequences) as the between-subjects factor. The Greenhouse–Geisser correction will be applied when Mauchly’s test indicates a sphericity violation (Huynh–Feldt for ε between 0.75 and 1), and the multivariate approach (Pillai’s criterion) will be reported in parallel as a sphericity-robust check. H1 and H2 will be tested with within-subjects trend contrasts across the autonomy gradient. Because acceptance need not fall in a straight line, the complete set of orthogonal polynomial contrasts—linear, quadratic, and cubic—is pre-specified, and each is reported together with the proportion of the omnibus effect it accounts for. A purely linear profile leaves the quadratic and cubic components negligible, whereas a step between two adjacent levels appears as a large linear component accompanied by a substantial quadratic or cubic one. Because every monotone step is linear-dominant, the polynomial decomposition establishes departure from a straight line but cannot by itself locate the break; the break is identified only from the Holm-corrected adjacent-pair contrasts (A–B, B–C, C–D). A quadratic-dominant profile with a small linear component would instead indicate a non-monotone pattern, which the hypotheses do not predict and which would be reported as such. A non-monotonic or threshold pattern will be reported as such rather than summarized by the linear trend alone. Post hoc comparisons use dependent-samples *t*-tests for the six scenario pairs with Holm’s sequential correction, applied within each hypothesis-defined family of tests in line with current guidance on multiplicity control [74]. Effect sizes will be reported as partial η^2^ for omnibus tests and Cohen’s dz for pairwise comparisons, with 95% confidence intervals, following effect-size-centered reporting recommendations [64]. Assumption checks include graphical inspection of difference-score distributions; as a distributional robustness analysis, the Friedman test with Holm-corrected Wilcoxon signed-rank pairwise comparisons will be reported alongside each primary test—supplemented by ordinal (cumulative-link) models as sensitivity analyses for the Likert-based outcomes [71]—and the concordance of parametric and nonparametric conclusions stated explicitly. Order dependence is tested directly as the scenario × sequence interaction; a non-significant interaction, together with equivalence of the four sequence-specific profiles, supports pooling across sequences. Independently of that test, the autonomy effect is re-estimated from a linear mixed model with random intercepts per participant and additive fixed effects of autonomy level and serial position (1–4). The Williams square renders this model identified, so the estimate is adjusted for arbitrary—not merely linear—serial-position and fatigue effects, while first-order carry-over is balanced by the design rather than modeled; position-adjusted and unadjusted estimates are reported side by side, and any material divergence between them is treated as evidence of an order artifact and interpreted accordingly. Perceived difficulty (DIF1) and perceived technical sophistication (MAN2) are each added as time-varying covariates in further sensitivity models, addressing fatigue and the possibility that responses track the apparent complexity of the system rather than its autonomy. Finally, between-person heterogeneity in response profiles is examined by adding a random slope for the linear autonomy contrast and testing the improvement in fit by a likelihood-ratio test; a substantial random-slope variance indicates that an average trajectory conceals distinct response patterns and licenses the exploratory typology described in Section 2.9.2. Because a non-significant test is not evidence of absence, a smallest effect size of interest of *dz* = 0.20—the value detectable at the Bonferroni bound for the six pairwise contrasts at *N* = 300—is fixed in advance, and equivalence testing by two one-sided tests against that bound is reported alongside every null pairwise result, so that any claim that two adjacent scenarios do not differ rests on an equivalence test rather than on the absence of significance.

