## 3. Expected Results

Based on the algorithm-aversion and trust studies [19,37,38], we expect acceptability and trust to decline—and perceived risk to rise—across the autonomy gradient from Scenario A to Scenario D, with the largest drop anticipated at the transition to autonomous planning (Scenario D), where the surgeon’s corrective role is described as residual. Whether that decline is a gradient or a step is an open question that the design is equipped to address: a step would show as a substantial quadratic or cubic component alongside the linear one, and its location would be identified by the adjacent-pair contrasts, which we expect to place the largest single drop at C–D. Nor do we assume the pattern is homogeneous across participants; a substantial random-slope variance would itself be informative, indicating that an average trajectory conceals distinct groups of respondents rather than describing a shared response. The expectation of decline is, in any case, consistent with survey evidence that public comfort is conditional on physician supervision [24,25,31]. For responsibility attribution, we expect the surgeon to be assigned the dominant share in low-autonomy scenarios [41], with a progressive migration toward the AI developer—and possibly a diffusion of responsibility across actors, indexed by falling Herfindahl concentration—as autonomy increases [44,45]. We expect the manipulation check (perceived AI control) to order the scenarios from A to D within each of the four presentation sequences, validating the experimental gradient independently of serial position, and we expect no scenario × sequence interaction. Should one nevertheless appear, the position-adjusted mixed-model estimate becomes the primary basis for interpreting H1–H3, and the magnitude of the order effect will itself be reported as a finding about the stability of vignette-based autonomy judgments. Given the design’s sensitivity (power of 0.99 against small within-subjects effects at ρ = 0.50, and 0.95 at ρ = 0.30, for the target sample), a null result for a primary hypothesis would place a tight upper bound on the size of any autonomy effect rather than leaving the question open; the pre-specified equivalence tests of Section 2.9.1 make that bound explicit rather than infer absence from non-significance [70]. The moderation hypothesis (H4) is powered only for medium-small interactions and will be interpreted with corresponding caution. Results will inform the ordering of public concerns along the assistance-to-autonomy continuum and identify which implementation configurations are publicly acceptable entry points for surgical AI in Romania.

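### Holm is valid for the six scenario pairs but slightly inefficient: Shaffer's sequential divisors keep family-wise error at 0.05 and every Holm rejection, with a small power gain for C–D

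*Protocol article*

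**What the plan says.** Section 2.9.1 of the protocol article analyses each composite "with autonomy level (four scenarios) as the within-subjects factor". It then compares all pairs by dependent t-tests "for the six scenario pairs with Holm’s sequential correction", with the correction working inside each family that a hypothesis defines. The polynomial contrasts are said to show departure from a straight line but not its location: "the break is identified only from the Holm-corrected adjacent-pair contrasts", that is A–B, B–C and C–D. Section 3 says of these adjacent contrasts: "which we expect to place the largest single drop at C–D". Table 5 repeats Holm for H1, for H2 and for the functional-form row. The Wilcoxon companion tests are also Holm-corrected, and Section 2.9.1 requires the agreement of parametric and nonparametric conclusions to be stated. Section 2.5 gives the pairwise sensitivity at N = 300 as dz = 0.16 uncorrected and dz = 0.20 at α/6.

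**The concern.** Holm divides α by 6, 5, 4, 3, 2, 1, as if any number of the six hypotheses could be true together. For equalities among four means that is impossible. If one pair differs, five or four true equalities cannot coexist, so Holm's second and third divisors guard against configurations that do not exist.

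The adjacent contrasts are the plan's only route to locating a break, so any avoidable strictness falls on the comparison that answers that question. What is at stake is a little power. Validity is not in doubt.

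**Working it through.** **Inputs.** From Section 2.5: "two-tailed significance threshold of α = 0.05 and a target power of 1 − β = 0.80"; "data collection continues until a minimum of 300 valid responses is reached"; and "Assuming a correlation between repeated measurements of ρ = 0.50". From Section 2.9.1: four scenarios, hence 4 × 3 / 2 = 6 pairs. With ρ = 0.50 the SD of a difference is σ√(2(1 − 0.50)) = σ, so dz equals the mean difference in units of the score SD.

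**The plan's own figures.** Paired t-test, noncentral t, df = 299, two-sided, power 0.80:
- α/6 = 0.00833 gives dz = 0.202 (stated 0.20). Power at exactly dz = 0.20 is 0.790.
- α = 0.05 gives dz = 0.162 (stated 0.16).

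Both reproduce.

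**Divisors.** Four means can be grouped in five ways, and each fixes how many of the six equalities are true:
- all four equal: 6
- three equal, one apart: 3
- two and two: 2
- one equal pair only: 1
- all different: 0

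The count can therefore only be 0, 1, 2, 3 or 6. At step j, with j − 1 hypotheses rejected, Shaffer divides α by the largest possible count not above 7 − j. For limits 6, 5, 4, 3, 2, 1 this gives **6, 3, 3, 3, 2, 1**. No divisor exceeds Holm's, so every Holm rejection is kept.

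For a 12-test family (two composites) the possible totals are 0 to 9 and 12. The divisors are 12, 9, 9, 9, 8, 7, … against Holm's 12, 11, 10, 9, 8, 7, …. The three adjacent equalities alone are logically free, so both methods give 3, 2, 1.

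**One step in isolation.** At the third step, α/4 (Holm) against α/3 (Shaffer) gives a minimum detectable dz of 0.194 against 0.188 at N = 300. The N needed for dz = 0.20 is 282 against 265, a difference of 17.

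**Simulation.** 20,000 studies per profile, multivariate normal, ρ = 0.50, six-test family. Power for C–D at N = 300:

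| Decline A–B / B–C / C–D (dz) | Holm | Shaffer | Gain (points) |
|---|---|---|---|
| 0 / 0 / 0.15 | 0.509 | 0.547 | 3.8 |
| 0 / 0 / 0.20 | 0.816 | 0.842 | 2.6 |
| 0 / 0 / 0.25 | 0.961 | 0.968 | 0.7 |
| 0.05 / 0.05 / 0.20 | 0.843 | 0.857 | 1.4 |
| 0.10 / 0.10 / 0.20 | 0.884 | 0.885 | 0.1 |
| 0 / 0.30 / 0.20 | 0.892 | 0.892 | 0 |

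A separate simulation gave 81.1% against 83.6% for the 0.20 step, a gain of 2.5 points.

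In the pure step of 0.20, A–D, B–D and C–D are equally large. C–D had the smallest, second or third smallest p-value in 33.0%, 32.4% and 31.0% of studies. The gain arises at the second and third places, where the divisor falls from 5 or 4 to 3.

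**Family-wise error (limit 0.05), Holm against Shaffer.** All means equal: 0.042 and 0.042. Step of 0.20 at D: 0.038 and 0.045. A = B and C = D, 0.20 apart: 0.033 and 0.036. No Holm rejection was lost in any simulated study.

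**Other families, step of 0.20, N = 300.** With acceptability and trust pooled (12 tests, correlation of 0.6 between composites assumed), C–D power is 0.749 against 0.752. With the three adjacent contrasts as their own family, it is 0.854 under either method.

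**The case against.** The strongest reply is that nothing here is wrong. Holm is valid, pre-specified and used consistently. The stated pairwise sensitivity is taken at α/6, the strictest step, and even in a pure step of dz = 0.20 Holm reaches about 81% against a target of 80%. All of that stands, so this is an improvement and not a correction.

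Four further objections limit its size:

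- **Profile.** A reader might infer that the gain of about 2.5 points applies to the profile the plan predicts. Section 3 expects decline across the whole gradient with the largest drop at D, and leaves gradient or step open. A flat A = B = C is the extreme that favours Shaffer.
- **Sample size.** At N = 140 the same step gives 0.409 against 0.444. That N is an analytic floor, and collection runs to at least 300.
- **Family.** Section 2.9.1 defines families by hypothesis, and H1 covers acceptability and trust. Table 5's per-composite wording points to six tests, so the reading is open. If the change also fixed six tests per composite, error control could loosen. With H1 read as 12 tests and the assumed correlation of 0.6, H1-wide error would rise from about 4.0% (Holm on 12) to 7.7% (Shaffer per composite) with all means equal. With the C–D step it would rise from 3.3% to 7.8%. The family must therefore not be redefined.
- **Concordance.** With Shaffer for the t-tests and Holm for the Wilcoxon tests, some disagreement could come from the divisors and not from distributional shape. This is a real but small cost.

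H1 and H2 themselves rest on the omnibus and trend tests, and the pairwise tests are called post hoc. The point therefore bears on locating the break, not on whether H1 or H2 is supported.

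**Conclusion.** The point holds as an optional refinement. For paired comparisons of means, Shaffer's procedure gives the same guaranteed 0.05 limit as Holm and never rejects less. Realised error moves closer to that limit.

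At N = 300 and ρ = 0.50 the C–D gain is about 2.5 points for a pure step of dz = 0.20 and nearly 4 points at dz = 0.15. It is 0 to 2 points when acceptance also falls before D, about 0.3 points in a 12-test family, and nil for a separate family of three adjacent contrasts. H2 covers risk only, so its six pairs form a six-test family, and the six-test figures apply there.

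These sizes assume normal scores and the planning correlation. The documents do not support reading this as a flaw in Holm or as a shortfall in the stated power.

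**What to change.** In Section 2.9.1 and the Table 5 rows for H1, H2 and functional form, replace Holm by Shaffer's sequential procedure for the dependent t-tests, within whatever hypothesis-defined family the plan uses. The divisors are 6, 3, 3, 3, 2, 1 for a six-test family such as H2, and 12, 9, 9, 9, 8, 7, …, 1 if H1 pools acceptability and trust. Do not redefine the family in the same edit.

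Keep Holm for the Wilcoxon comparisons, whose null hypotheses need not be transitive, and for RES5/RES6. Where parametric and nonparametric conclusions are compared, also print the Holm-adjusted t-test p-values, so that any disagreement is not due to the divisors.

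The cost is one line of text, the matching table entries and one extra column of p-values. Sample size is unchanged. So is the stated dz = 0.20 for a six-test family, because the first divisor is still 6. The change is best made before pre-registration; afterwards Section 2.12 would require it to be reported as a deviation.

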## 2. Materials and Methods

### 2.1. Study Design

This is a cross-sectional, vignette-based experiment with a four-level within-subjects (repeated-measures) design. Vignette experiments combine the internal validity of experimental manipulation with survey feasibility and are an established method for isolating drivers of health-related judgments [61]; their design and analysis follow current methodological guidance for vignette data [62]. Each participant reads and evaluates all four scenarios of AI implementation (A–D), presented in a counterbalanced sequence. The within-subjects structure makes each respondent their own control, eliminating inter-individual variability from between-scenario comparisons and substantially increasing statistical power relative to a between-subjects design of the same size [63]. The presentation sequence is counterbalanced. The survey platform allocates participants at random, in equal proportions and independently of any participant characteristic, to one of the four sequences of a Williams (balanced Latin-square) design: A → B → C → D, B → D → A → C, C → A → D → B, and D → C → B → A. In this square, every scenario occupies every serial position exactly once, and every ordered pair of scenarios occurs exactly once, so that autonomy level is orthogonal both to serial position and to first-order carry-over, and an additive model containing a four-level autonomy effect and a four-level serial-position effect is fully identified. The theoretically motivated ascending sequence and its exact mirror image are retained as two of the four arms. A fixed ascending presentation would have mirrored the progressive continuum under investigation and given every participant an identical evaluation context, but it would have left order, carry-over, and fatigue effects inseparable from the autonomy gradient; because H1–H3 concern precisely that gradient, internal validity was given priority over uniformity of context. Counterbalancing also makes the embedded manipulation check diagnostic rather than merely descriptive: perceived AI control should track the described autonomy level within every sequence, whereas an anchoring or fatigue artifact would instead track serial position—a distinction that a monotonic manipulation-check profile obtained under a fixed order cannot draw. Presentation sequence is therefore retained as a between-subjects factor in all primary models, a second manipulation check (perceived technical sophistication) separates autonomy from technical complexity, and a per-scenario difficulty item indexes fatigue (Section 2.6, Section 2.7, Section 2.8, and Section 2.9.1). The study involves no medical, pharmacological, or surgical intervention. Reporting of the completed study will follow current recommendations for effect-size-based reporting [64] and, for the web-survey component, the CHERRIES checklist as operationalized in recent methodological guidance [65]. Publication of the protocol in advance of data collection is intended to reduce publication bias and analytic flexibility [66,67].

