
The recruitment target is *N* = 300 valid participants. This target is dictated not by the within-subjects effects (for which power at *N* = 300 is 0.99 for small effects at ρ = 0.50, with a minimum detectable effect of *f* = 0.07), but by the person-level analyses: the familiarity moderation (minimum detectable interaction *f*^2^ = 0.037 at *N* = 300), the global preference test (minimum detectable *w* = 0.21 on 5 degrees of freedom), and descriptive analyses of demographic subgroups. A small interaction effect (*f*^2^ = 0.02) would require *N* ≈ 550; H4 therefore remains partially exploratory, and a non-significant result will not be interpreted as evidence of absence. At *N* = 300, dependent pairwise comparisons detect differences from *dz* = 0.16 (uncorrected) and *dz* = 0.20 (at the Bonferroni bound for six pairwise comparisons), so all six scenario contrasts can be treated as confirmatory. Counterbalancing entails no loss of sensitivity for the primary comparisons: with sequence entered as a four-level between-subjects factor, the autonomy main effect retains 3 degrees of freedom and the same noncentrality, so the minimum detectable effect at *N* = 300 remains *f* = 0.07. The scenario × sequence interaction—the direct test of order dependence—carries 9 degrees of freedom and a minimum detectable effect of *f* = 0.08 at ρ = 0.50 (*f* = 0.10 at ρ = 0.30), giving power of 0.95 against a small order effect of *f* = 0.10; the serial-position main effect in the additive model carries 3 degrees of freedom and matches the sensitivity of the autonomy effect itself. Order artifacts large enough to masquerade as the hypothesized autonomy gradient are therefore detectable, rather than being assumed away. In the pilot, by contrast, the ascending and descending arms (*n* = 25 each) bound order effects only at *f* = 0.17, which excludes medium-to-large artifacts but not small ones; the definitive test is the main-study interaction. Table 2 summarizes the power analysis, and Figure 1 shows achieved power as a function of the number of valid responses.

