Several limitations are accepted by design and will be declared in the results article. First, the sample is a self-selected online convenience sample: results describe Romanian adults active in digital environments—likely younger and more educated than the general population—and do not support national generalization; the sample structure will be reported against National Institute of Statistics reference data. Second, the vignettes are hypothetical, and the distance between a vignette judgment and a decision taken in a consulting room is not merely one of degree. Participants evaluate a scenario in which they are not injured, not in pain, not facing a scheduled operation, and not choosing between real surgeons. They bear no consequences for the judgment they record, receive no counseling, and cannot ask questions. Above all, they are not exposed to the most influential element of real surgical decision-making: a conversation with the clinician who would operate, whose endorsement and explanation are known to shift acceptance of AI-supported care substantially [27,28]. Stated acceptability under these conditions is best read as a measure of prior disposition toward a described scenario rather than as a prediction of consent behavior. The ordering of the scenarios is likely to be more robust than the absolute levels, which could be lower than those a counseled patient would report or higher if hypothetical risk is discounted. This is a standard limitation of vignette methodology [61,62], and the remedies lie outside the present design: replication among patients actually scheduled for facial reconstructive surgery, and ultimately observation of consent decisions where such systems are in use. Third, presentation sequence is counterbalanced but not thereby rendered irrelevant. The Williams square balances serial position and first-order carry-over, so that the autonomy effect is estimable free of both, but no four-sequence design balances higher-order carry-over—a participant’s evaluation of the third scenario being shaped jointly by the first two—and contrast effects that depend on which scenario was seen immediately before therefore remain possible. The scenario × sequence interaction, the position-adjusted model, and the difficulty covariate bound the magnitude of what remains; they do not remove it, and a large residual would warrant a between-subjects replication in which each participant evaluates a single scenario. Fourth, demand and contrast effects are inherent to within-subjects designs: seeing all scenarios, participants may infer the study objective and exaggerate differentiation between scenarios; comparisons remain internally valid, but absolute difference magnitudes warrant caution. Fifth, all measures share a common method and a single measurement occasion, in a rapidly evolving attitude domain [38]. Sixth, the survey platform does not record completion time, so quality control relies on embedded checks rather than temporal filters [69]. Seventh, the demographic and familiarity subgroups formed within a convenience sample of 300 will differ substantially in size, and several will be small; the minimum-cell rule of Section 2.9.2, and the requirement that subgroup differences be inferred only from formal interaction terms, are intended to forestall the familiar error of asserting a difference from a significant effect in the larger subgroup together with a non-significant one in the smaller. None of these limitations is unusual for online vignette experiments, and declaring them in advance is intended to keep the eventual findings interpretable at their proper scope.

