H4. moderation by AI familiarity (partially exploratory)	RM-ANCOVA or linear mixed model with random intercepts: scenario (within) × B1 (centered), sequence between	F (or likelihood-ratio test), *p*, *f*^2^; simple slopes with 95% CI
Global preference (P1)	Goodness-of-fit chi-square over 6 analysis categories (2 undecided options pooled); standardized residuals; consistency with maximum-acceptability scenario, descriptive	χ^2^, *df*, *p*, *w*; standardized residuals
Predictors of acceptability	Person-level multiple regression: mean acceptability on familiarity, general attitudes, demographics	*B*, *SE*, β, 95% CI, R^2^, VIF
P2, P4a/P4b (exploratory)	Brief thematic analysis (P2); descriptive statistics, within-person P4a–P4b difference, and correlations with RES5/RES6	Theme frequencies; Pearson/Spearman *r*
Order dependence (design validation)	Scenario × sequence interaction in the mixed RM-ANOVA; position-adjusted linear mixed model (autonomy + serial position, random intercepts)	*F*, corrected *df*, *p*, partial η^2^ (90% CI); adjusted vs. unadjusted scenario means
Functional form of the autonomy effect	Orthogonal polynomial contrasts (linear, quadratic, cubic); Holm-corrected adjacent-pair contrasts	*F*, *p*, partial η^2^ per contrast; share of the omnibus effect
Autonomy vs. technical complexity	Mixed RM-ANOVA on MAN2 (sequence between); primary models re-estimated with MAN2 as a time-varying covariate	*F*, corrected *df*, *p*, partial η^2^; adjusted scenario means
Between-person heterogeneity (exploratory)	Random-slope linear mixed model; latent-class growth analysis of individual trajectories	Likelihood-ratio χ^2^, *p*; random-slope SD; class sizes, BIC, entropy

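### The 9-df order test has low power for a steeper autonomy slope in the two autonomy-ordered arms, and position adjustment cannot reveal that pattern; a pre-specified 1-df contrast should be added

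*Protocol article*

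**What the plan says.** Participants are randomised to four Williams sequences. Section 2.1: "The survey platform allocates participants at random, in equal proportions and independently of any participant characteristic". Two of the four follow the autonomy order: "The theoretically motivated ascending sequence and its exact mirror image are retained as two of the four arms". The other two, B-D-A-C and C-A-D-B, are scrambled.

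Section 2.9.1 sets the order test: "Order dependence is tested directly as the scenario × sequence interaction". The Order dependence row of Table 5 repeats it: "Scenario × sequence interaction in the mixed RM-ANOVA; position-adjusted linear mixed model (autonomy + serial position, random intercepts". Section 2.5 gives this interaction 9 df, a minimum detectable f of 0.08 at ρ = 0.50, and power of 0.95 at f = 0.10. It concludes: "Order artifacts large enough to masquerade as the hypothesized autonomy gradient are therefore detectable, rather than being assumed away".

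The supporting safeguards are:
- equivalence of the four sequence profiles, required for pooling, with no bound or test stated (2.9.1);
- a comparison of position-adjusted with unadjusted autonomy estimates, in which a material divergence counts as an order artifact (2.9.1);
- profiles by sequence, and the interaction effect size with its 95% CI (2.9.2, item ix);
- a pilot comparison of the ascending and descending arms (2.8).

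If an interaction appears, section 3 makes the position-adjusted estimate the main basis for interpreting H1–H3.

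**The concern.** H1 and H2 concern the slope over autonomy levels. An order effect that bears directly on that slope is one that makes it steeper when the progression from A to D (or D to A) is visible. The design can examine this with a single contrast, ordered against scrambled arms. The plan spreads it over 9 df and quotes power only for an order effect as large as the whole small gradient.

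At stake is partial inflation. The pooled trend would be reported as the autonomy effect while part of it came from half the sample seeing the scenarios in sequence, and a non-significant interaction would count in favour of pooling.

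**Working it through.** **Inputs.** Section 2.5: "two-tailed significance threshold of α = 0.05 and a target power of 1 − β = 0.80"; "The recruitment target is *N* = 300 valid participants"; ρ = 0.50, with 0.30 as the conservative value; small effect f = 0.10. Equal allocation gives 75 per sequence, 150 per pair of arms. The share of the gradient that is order-driven is an assumption, because the documents give none.

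**Plan's figure.** With m = 4 scenarios, λ = N·m·f²/(1 − ρ), df1 = 9 and df2 = (300 − 4)·3 = 888. For f = 0.10 and ρ = 0.50, λ = 300·4·0.01/0.5 = 24 and power is 0.952. The stated 0.95 reproduces. The same convention reproduces the minimum detectable effects (0.081 at ρ = 0.50, 0.096 at ρ = 0.30).

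**What f means for this pattern.** Let g be the pooled slope, with slopes (1 + e)g in the ordered arms and (1 − e)g in the scrambled arms. Every arm deviates from g by ±e·g, all of it linear, so the interaction f equals e times the gradient f. For a gradient of f = 0.10, an interaction of f = 0.10 needs e = 1: slope 2g in the ordered arms and zero in the scrambled arms. If half the pooled gradient is order-driven, e = 0.5: slopes 1.5g and 0.5g, a ratio of three, with interaction f = 0.05.

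**Power for the half-gradient case, N = 300:**

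| Gradient f | ρ | Interaction f | λ | 9-df test | 1-df contrast |
|---|---|---|---|---|---|
| 0.10 | 0.50 | 0.05 | 6.0 | 0.34 | 0.69 |
| 0.10 | 0.30 | 0.05 | 4.3 | 0.24 | 0.54 |
| 0.15 | 0.50 | 0.075 | 13.5 | 0.72 | 0.96 |
| 0.20 | 0.50 | 0.10 | 24.0 | 0.95 | 0.998 |

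A simulation of the first row (10,000 runs) gave 0.331 and 0.683. The pooled linear trend was significant in 99.9% of runs; in 66.8% it was significant while the 9-df test was not.

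**Position adjustment.** With equal numbers per sequence, serial position is orthogonal to autonomy. Fitting the arm means of the first row with and without position gave the same scenario effects relative to A (−0.089, −0.179, −0.268), and every position coefficient was zero. The divergence check therefore cannot respond to this pattern, and moving to the adjusted estimate leaves the pooled slope unchanged.

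**Pilot.** It contains only the two ordered arms, so steepening common to both cancels in their comparison.

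**Profile equivalence.** If the dz = 0.20 bound from 2.9.1 were borrowed (an assumption), the 90% CI half-width between two arms of 75 would be 1.645·√(2/75) = 0.27. That exceeds the bound, so equivalence could not be shown.

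**Does the 1-df contrast respond to fatigue?** With linear codes −3, −1, 1, 3 for A to D, added over the ordered arms and subtracted over the scrambled arms:
- position 1: −3 + 3 + 1 − 1 = 0
- position 2: −1 + 1 − 3 + 3 = 0
- position 3: 1 − 1 + 3 − 3 = 0
- position 4: 3 − 3 − 1 + 1 = 0

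Additive position effects cannot trigger it.

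**Does it respond to carry-over?** Yes. Code A to D as −1.5, −0.5, 0.5, 1.5 (sum of squares 5), and let each response shift by c times the code of the preceding scenario. The slope shifts by 1.25c/5 = +0.25c in A-B-C-D and in D-C-B-A, and by −3.75c/5 = −0.75c in B-D-A-C and in C-A-D-B. The scrambled arms are distorted three times as much, in the opposite direction.

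**The case against.** An omnibus interaction is a standard order test and has the advantage of covering many patterns. If only the ascending arm is steeper and this again makes up half of an f = 0.10 gradient, the slopes are 2.5g once and 0.5g three times. The interaction f is then 0.10·√0.75 = 0.087 and 9-df power is 0.86, against 0.69 for the 1-df contrast. This stands, and it is why the omnibus test must stay.

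The half-gradient case is chosen. At f = 0.10 the pooled A–D difference is dz = 0.27, so the artifact adds about 0.13, below the plan's smallest effect of interest (0.20), and a true gradient in the hypothesised direction remains. This stands as a limit on severity.

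The plan does not rest on a p-value alone. It also asks for profile equivalence and reports profiles by sequence, and its third limitation concedes that the checks do not remove residual order effects. That is fair, but neither the descriptive profiles nor a CI on a 9-df effect size estimates the ordered-minus-scrambled slope difference.

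Some stronger readings are tempting and are not supported. A reader might infer that the sentence on masquerading artifacts in 2.5 is false; for an artifact as large as the whole small gradient it is right. A reader might take the fourth limitation, "participants may infer the study objective and exaggerate differentiation between scenarios", to name this mechanism. It describes people who have seen all the scenarios, which is everyone in all four arms; stronger exaggeration in the ordered arms is a plausible extension and is not stated. Nor does the plan commit to reporting an absence of order dependence.

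**Conclusion.** The concern holds in limited form. The plan's arithmetic is correct and the design sound, but its formal order test is weak against one specific pattern: partial steepening of the slope in both autonomy-ordered arms. With N = 300, ρ = 0.50, a gradient of f = 0.10 and half of it order-driven, 9-df power is 0.34 (0.24 at ρ = 0.30). Missing the artifact in about two studies of three applies to that case only and is not a general miss rate: the test reaches 0.72 at f = 0.15 and 0.95 at f = 0.20. The result assumes equal steepening in both ordered arms and balanced sequences.

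The firmer part does not depend on the assumed share. Under balance, position adjustment can neither detect nor correct this pattern, although 2.9.1 and section 3 rely on it as check and fallback. Severity is minor to moderate.

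**What to change.** - **Section 2.9.1 and the Order dependence row of Table 5:** for each primary composite, pre-specify one 1-df contrast, linear autonomy trend × (A-B-C-D and D-C-B-A versus B-D-A-C and C-A-D-B). Report the slope in each pair of arms and their difference with a 95% CI. Keep the 9-df interaction as the omnibus test for other patterns.
- **Section 2.5:** limit the sentence on masquerading artifacts to those as large as the whole small gradient, and state that partial inflation is detected with lower power.
- **Sections 2.9.1 and 3:** state that, under balanced allocation, position adjustment cannot detect or remove a slope difference between ordered and scrambled arms.
- **Interpretation:** do not present the scrambled-arm slope as the artifact-free gradient, given the carry-over result above.

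The cost is some wording and one contrast per composite from a model already planned, with no new data. It adds one design-check p-value per composite, and at f = 0.10 the contrast still falls short of 80% power in the half-gradient case, so the CI is its main product. Pre-registration and data collection have not begun, so it can still be specified in advance.
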